#### Data collection procedures

All data are collected in a central REDCap database housed at NCH. To minimize variation and improve the consistency of the interpretation of clinical information, we utilize standardized data collection forms with established definitions for all variables. Outcome assessors are blinded to the primary outcome at the 6 months and 1 year time points. Unblinding will only take place in the event of a clinical emergency.

### Statistical considerations

#### Sample size and power

The sample size needed to assess the primary outcome of the proportion of patients with recurrent pilonidal disease at 1 year is based on (1) previous published studies and institutional data on pilonidal disease recurrence rates and (2) the efficacy of laser hair depilation treatment to reduce pilonidal disease recurrence in previous studies and our institutional pilot study. In this RCT, the recurrence rate within 1 year is expected to be a minimum of 12% in the control group and a maximum of 2% in the laser group. Based on these estimated recurrence rates, under a group sequential design with one interim and one final analysis, an overall type I error rate (two-sided) of 5%, and power of 80%, the sample size required for this trial is 122 patients in each treatment group. Assuming a 10% drop-out rate over the course of the 1 year follow-up, we will plan to enroll 136 patients in each group for a total of 272 patients.

#### Planned interim analysis

An interim analysis is planned when one quarter of the planned total patients (34 patients in each group) have completed their 1 year follow-up, and a final analysis will be performed when all patients have completed 1 year of follow-up. These two analyses have been unequally spaced in order to ensure that the interim analysis is performed before study enrollment is complete.

Throughout the trial, the rate of pilonidal disease recurrence at 6 months and 1 year and the tolerance of laser treatments are monitored for safety. Tolerance to the laser treatments is monitored by examining for study-related serious adverse events (SAEs), which include severe pain (defined as a maximum pain score of 8 or above during or within 24 h of treatment) or second degree burns. The rates of SAEs are calculated after every group of 10 patients has completed the course of treatment. The percentage of patients with either a second degree burn or a maximum pain score of 8 or above during or after treatment is estimated. If the lower 95% confidence limit of this proportion exceeds 10%, the trial will be stopped. The 10% level was chosen based on input from patients involved in our feasibility and tolerability pilot in which they expressed that even if they had experienced acute pain or a minor burn, they would likely continue receiving therapy, as these both are self-limited events with minimal long-term morbidity. These rates are regularly reported to the Data and Safety Monitoring Committee (DSMC).

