#### Intervention group

Similar to the control group, the patients and families in the intervention group are taught hair removal techniques at the initial visit and asked to perform either chemical or mechanical depilation as needed to keep the area hair-free between clinic treatments. Fitzpatrick skin type classification is assessed at the first treatment visit and used to select the best laser to perform hair removal for each patient [7–17, 23]. A 7% lidocaine/7% tetracaine cream is applied 45 min prior to treatment to minimize any discomfort associated with the heat of the laser treatments. Patients receive either an 810 nm (for Fitzpatrick skin types I–IV) or Nd:YAG (for Fitzpatrick skin types V–VI) 28 joule application at auto pulse duration for 400 ms. Subjects randomized to the laser depilation arm visit the surgery clinic for one treatment every 4–6 weeks to receive a total of five treatments. The energy settings of the laser are sequentially increased at each visit in order to maximize the depilation effect.

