#### Post laser treatment follow-up

Immediately following each laser treatment and 24 h after, the patient is asked to rate their pain from 1 to 10 utilizing the numeric rating scale (NRS). The immediate postprocedure pain score is obtained in person at the conclusion of the laser procedure, while the 24 h pain score is communicated to the study team by text message, email, or phone call the following day.

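### The laser safety stopping rule is triggered by course completion and uses a maximum pain score that the two described ratings may not capture, so its signal can be delayed or lowered.

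*Protocol article*

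**What the plan says.** The rule is in the protocol article, Planned interim analysis. Its timing is: "The rates of SAEs are calculated after every group of 10 patients has completed the course of treatment". The quantity is: "The percentage of patients with either a second degree burn or a maximum pain score of 8 or above during or after treatment is estimated". The action is: "If the lower 95% confidence limit of this proportion exceeds 10%, the trial will be stopped". The confidence interval method is not named.

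The same section defines the pain component as "severe pain (defined as a maximum pain score of 8 or above during or within 24 h of treatment". Two sentences later the window is worded differently, as during or after treatment, with no 24 h limit.

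Pain collection is described under Post laser treatment follow-up: "Immediately following each laser treatment and 24 h after, the patient is asked to rate their pain from 1 to 10". The first of these is a point rating: "The immediate postprocedure pain score is obtained in person at the conclusion of the laser procedure". The second is reported the next day by text, email or phone.

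Under Intervention group, the course is "one treatment every 4–6 weeks to receive a total of five treatments".

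**The concern.** A tolerance rule should be most sensitive to the patients who tolerate treatment worst, and these are the patients most likely not to finish five sessions. Tying the calculation to completion means that they do not bring the next look closer. If the percentage is also taken over completers, their events are lost from it.

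The pain component has a separate problem. The rule needs the highest score over a window that includes the session itself. The ratings described are taken at the end of the session and a day later. The larger of two point ratings can equal the peak over the window but cannot exceed it.

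Both problems push the same way, towards a later or weaker signal. This is the only numerical criterion in the article for stopping the trial on tolerance, and participants include minors.

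**Working it through.** **Event definition against data collection.**
- Needed: the maximum over the session and the next 24 h in one sentence, and over the session and an open-ended period afterwards in another.
- Described: one rating at the end of the procedure and one at 24 h, at each of up to five sessions.
- Not described: a rating during the session, or a question about the worst pain since the session.

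The two sections do not match, and neither do the two wordings of the window. The documents give nothing from which to size this part.

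**Timing of the first look.** Five sessions 4-6 weeks apart take (5 − 1) × 4 = 16 to (5 − 1) × 6 = 24 weeks, or about 3.7 to 5.5 months. Trial status reports over 50 patients enrolled between September 2017 and 25 October 2018. Taking 50 in about 13.5 months, constant accrual and 1:1 allocation, the laser arm gains 50 / 13.5 / 2 = 1.85 patients per month. The 10th laser patient enrols at 10 / 1.85 = 5.4 months. If nobody stops early, the 10th completion falls at about 9.1 to 10.9 months, with 1.85 × 9.1 = 17 to 1.85 × 10.9 = 20 patients in the laser arm. Each early stopper delays it further.

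**Stopping boundaries.** The article gives no operating characteristics for this rule, so there is no stated figure to reproduce. I took cumulative looks at n = 10, 20, ..., 130 and found the smallest event count whose lower two-sided 95% limit exceeds 10%.
- Exact (Clopper-Pearson): 4, 6, 8, 9, 10 events at n = 10 to 50. At n = 10, 3 events give a lower limit of 6.7% and 4 events give 12.2%.
- Wilson: 3, 5, 7, 8, 10 events. At n = 10, 2 events give 5.7% and 3 events give 10.8%.

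**Effect of counting completers only.** Let p be the true event rate among all patients treated, and q the share of patients with an event who leave before the fifth session. Assume that patients without an event all complete. The rate among completers is

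p(1 − q) / (1 − pq).

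For p = 0.20 and q = 0.50 this is 0.10 / 0.90 = 11.1%. The chance of crossing a boundary follows by exact recursion over the looks. Ranges run from exact to Wilson limits.

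| q | Completer rate | Stop by n = 50 | Stop by n = 130 |
|---|---|---|---|
| 0 | 20.0% | 60-70% | 92-96% |
| 10% | 18.4% | 48-60% | 84-90% |
| 25% | 15.8% | 30-43% | 60-73% |
| 30% | 14.9% | 25-37% | 50-64% |
| 50% | 11.1% | 7-16% | 12-24% |

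A separate simulation with 136 patients treated, in which early stoppers reduce the number of completers available, gave 59-72% at q = 25% and 12-23% at q = 50%. With p = 30% and q = 30%, the chance of stopping by n = 130 is about 99%, so the loss is small when the true rate is far above the limit.

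**The case against.** The strongest reply is that the completion sentence says when a calculation is run, not who is in it. The next sentence speaks only of a percentage of patients. A reader might infer that the rule excludes early stoppers by definition, but the article does not state this. Completion is expressly the trigger and only by inference the denominator. That part of the reply stands. It does not remove the trigger problem, and completers are the only group the section names.

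A reader might also infer that the maximum pain score is not collected at all. That is too strong. Two ratings per session over up to five sessions yield a maximum, and Safety monitoring adds pain scores under the nursing protocol. Those scores are given no timing and are not linked to the rule, so the mismatch remains, but it is narrower. Second degree burns need no pain score.

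A third inference is that the rule will miss the patients it is meant to detect. That depends on q, which is not given. The only relevant evidence, the pilot patients' statement that they would likely continue after acute pain or a minor burn, suggests that q may be low. At q = 0 the two denominators agree.

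Finally, under Safety monitoring a surgeon sees each patient before and after every treatment, the principal investigator learns of adverse events as they occur, adverse events are reviewed quarterly, and the monitoring committee meets every 6 months. A burned patient who withdraws is therefore visible. This is case reporting, though, and it does not correct the proportion on which the numerical rule acts.

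**Conclusion.** The concern holds in a limited form. Two things follow from the text: early stoppers do not advance the count, and the described ratings do not match the definition of the event. That early stoppers are also left out of the percentage is the natural reading, not a stated rule.

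Under that reading and an assumed true rate of 20%, the chance of stopping over all looks falls from 92-96% to 84-90% if one affected patient in ten stops early, to 60-73% if one in four does, and to 12-24% if half do. These figures rest on assumed values of p and q, cumulative looks, two-sided limits and complete follow-up of unaffected patients. The loss from missed peak pain comes on top and cannot be sized from the documents.

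This should be fixed. It is not evidence that the rule has failed or will fail.

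**What to change.** 1. State that the percentage is taken over every patient who has received at least one laser session, with early stoppers counted, and run a look at each 10th patient treated.
2. At the two existing pain contacts, ask for the worst pain during the session and the worst pain since the session.
3. Reconcile the two wordings of the pain window in Planned interim analysis with each other and with Post laser treatment follow-up.

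The 8-point and 10% thresholds are left unchanged.

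The cost is one sentence on the denominator and trigger, one aligned definition and two reworded questions, with no extra contacts. The drawback is that the percentage then mixes patients partway through the course with those who have finished it, so the rate per session should be shown beside it. Enrollment is already open, so sessions before the change will have only the two point ratings, and reports to the monitoring committee should say so.

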#### Analysis methods

All patient baseline demographics and clinical characteristics will be described and summarized overall and between treatment groups. The balance in these characteristics across treatment groups will be studied and reported. Data on all pre-treatment characteristics (including demographics, race, ethnicity, socioeconomic variables, body mass index (BMI), clinical characteristics, laboratory values, previous episodes of disease, and previous procedures performed) will be collected from the patient, caregiver, and medical record at the time of enrollment. This will allow robust data capture with minimal missing data.

#### Analytic plan

The means/medians and standard deviations/interquartile ranges of all baseline demographic and clinical variables will be evaluated in the total study sample and will be compared between groups using *t* test or Mann-Whitney *U* tests for continuous variables and chi-square tests for categorical variables. For the primary outcome of recurrence within 1 year, we will calculate this proportion and its 95% confidence interval using the Wilson method in both groups and compare this proportion between groups using a Fisher exact test. All outcome comparisons will be conducted using an intention-to-treat (ITT) analysis approach, wherein patients’ data are analyzed according to their randomized treatment assignment. This analysis is hypothesis-driven with an expected decrease in the rate of pilonidal disease recurrence from 12% in the control group to 2% in the laser group.

Heterogeneity of treatment effects will be evaluated for both primary and secondary outcomes across four factors of interest: episodes of previous disease (1, 2, ≥ 3 episodes), previous surgical excision performed (yes/no), gender (male/female), and BMI (under or normal weight vs. overweight or obese). Treatment effect heterogeneity will be explored by evaluating these factors as potential effect modifiers by including each in a model to include the main treatment effect, the main factor effect, and the interaction term for the treatment by factor [25]. Treatment effects will be estimated for each level of the factor and compared across these groups. Identification of effect modification will be made through tests of interaction in these models, which control the family-wise error rate of each of these comparisons at the 1% level (translating to a maximum family-wise error rate of 9%).

Analyses of secondary outcomes will also follow an ITT approach. Categorical secondary outcomes (e.g., complications) will be assessed using estimated proportions and confidence intervals and compared between groups using Fisher exact tests or Pearson chi-square tests as appropriate, similar to the primary outcome. Continuous secondary outcomes (e.g., HRQOL) will be assessed using medians and interquartile ranges and compared between groups using Mann-Whitney *U* tests. These are hypothesis-driven analyses, with the laser group expected to have less disability for both the patient and caregiver, higher HRQOL scores, higher healthcare satisfaction scores, more favorable disease-related attitudes and perceived stigma, lower rates of pilonidal disease-related complications, lower rates of incision and drainage, lower rates of surgical excision, lower rates of postoperative complications, and higher compliance with treatment. We will give specific consideration to the potential for varying treatment effects across groups defined by the four patient characteristics described in the preceding paragraph. In further exploratory analyses, we will examine the complete longitudinal trajectory of both patient- and guardian-reported HRQOL, satisfaction with healthcare, and disease-related attitudes and perceived stigma through the use of linear mixed effects models [26]. In addition, both primary and secondary endpoints will be examined, though not formally statistically compared, across various subgroups defined by patient socioeconomic status (SES) and demographic characteristics, including race, ethnicity, insurance status, household annual income, and number of household residents. These subgroup analyses will be exploratory rather than confirmatory.

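### Fisher's exact test is valid for the primary outcome but leaves part of the allowed 5% unused; Boschloo's exact test and an overall risk difference with a confidence interval would be a cheap improvement

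*Protocol article*

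**What the plan says.** The protocol article, Analytic plan, fixes the primary analysis in one sentence: "we will calculate this proportion and its 95% confidence interval using the Wilson method in both groups", and then "compare this proportion between groups using a Fisher exact test". No overall risk difference, risk ratio or odds ratio with an interval is named for that comparison. The next paragraph plans models with a treatment-by-factor interaction for primary and secondary outcomes, and estimates treatment effects at each level of four factors.

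Sample size and power sets the frame: rates "expected to be a minimum of 12% in the control group and a maximum of 2% in the laser group", a plan "under a group sequential design with one interim and one final analysis", and "an overall type I error rate (two-sided) of 5%, and power of 80" percent. From these it concludes that "the sample size required for this trial is 122 patients in each treatment group". After "Assuming a 10% drop-out rate over the course of the 1 year follow-up" the target is 136 per arm. The section names neither the test used for sizing nor the interim boundary.

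**The concern.** Fisher's test conditions on the total number of recurrences. With few events, few tables are possible for a given total, so the achieved error can sit well below the nominal level. Recurrence here is expected between 2% and 12%, where this effect is marked. An unconditional exact test can use more of the allowed error and still guarantee the limit.

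The second matter is what a reader receives. The trial asks how far laser treatment reduces recurrence, but the named primary outputs are two one-sample intervals and a p-value. Two per-arm intervals are not an interval for the difference, and in borderline results they can overlap beside a significant p-value.

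At stake are a few points of power and a primary result without a stated precision for the effect. Control of the type I error is not at stake.

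**Working it through.** **Inputs.** From Sample size and power: 12% v 2%, two-sided 5%, 80% power, 122 evaluable and 136 enrolled per arm. From Planned interim analysis: one look at 34 per arm. From Analytic plan: Fisher's test and Wilson intervals. Assumptions of this check: the interim boundary (a range is shown) and the smaller effect of 12% v 3%.

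**1. The plan's own sample size.** With pooled rate 0.07,

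n = [1.96·√(2·0.07·0.93) + 0.8416·√(0.12·0.88 + 0.02·0.98)]² / 0.10² = 101.0, so 102.

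The continuity-corrected value is (n/4)·[1 + √(1 + 4/(n·0.10))]² = 120.2, so 121. An O'Brien-Fleming-type look at one quarter of the information multiplies this by about 1.0002: 121 × 1.0002 = 121.02, so 122. Then 122/0.9 = 135.6, so 136. Other variants miss 122: pooled 102, unpooled 99, arcsine 88, pooled with Pocock 118. The stated size therefore fits a Fisher-like calculation, although the article does not say so.

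**2. Fisher's actual size.** Sum the product of the two binomial probabilities over all tables with Fisher p ≤ 0.05, using the same rate in both arms.

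| Common rate | 122 per arm | 136 per arm |
|---|---|---|
| 2% | 0.8% | 1.0% |
| 7% | 2.5% | 2.7% |
| 12% | 3.1% | 3.3% |
| Maximum over rates | 3.8% | 3.9% |

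**3. Boschloo's test.** It ranks tables by Fisher's p-value and takes the largest cut-off whose size, maximised over the common rate, is at most 5%. At 122 per arm the cut-off is 0.0657 (maximum size 4.995%). Since 0.0657 exceeds 0.05, every table that Fisher rejects is also rejected. Its size at a 12% common rate is 4.2%.

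An example of a table on which they differ is 9/122 v 2/122. With equal arms, the two-sided Fisher p is 2·[C(122,9)·C(122,2) + C(122,10)·C(122,1) + C(122,11)]/C(244,11) = 0.060. Fisher does not reject; Boschloo does.

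**4. Power, single look at 5%.**

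| Rates | n per arm | Fisher | Boschloo |
|---|---|---|---|
| 12% v 2% | 122 | 84.5% | 87.9% |
| 12% v 2% | 136 | 89.1% | 91.3% |
| 12% v 3% (assumed) | 122 | 70.4% | 75.5% |
| 12% v 3% (assumed) | 136 | 76.6% | 80.0% |

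The Pearson chi-square reaches 90.5% at 122 per arm for 12% v 2%, but its size can reach about 5.2%. Boschloo is therefore the fair comparator.

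**5. The interim look.** With a look at 34 per arm and 122 at the end, Fisher's power is 84.5% under an O'Brien-Fleming-type boundary, 82.9% under Pocock-type spending and 78.7% under constant Pocock bounds. At final-look alphas from 0.03 to 0.045, Boschloo still gains about 2 to 3 points; at 0.03, for example, it has 82.8% v 80.3%.

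**6. The interval for the difference.** Newcombe's limits use the Wilson limits (l, u) of each arm:

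lower = d − √[(p₁ − l₁)² + (u₂ − p₂)²]; upper = d + √[(u₁ − p₁)² + (p₂ − l₂)²].

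- 10/122 v 2/122 (Fisher p = 0.034): the Wilson intervals, 4.5–14.4% and 0.5–5.8%, overlap. The difference is 0.0656, with lower limit 0.0656 − √(0.0368² + 0.0414²) = 0.010 and upper limit 0.0656 + √(0.0624² + 0.0119²) = 0.129. That is 6.6 points (1.0 to 12.9).
- 15/122 v 2/122: the Wilson intervals, 7.6–19.3% and 0.5–5.8%, do not overlap. The difference is 10.7 points (4.4 to 17.8).

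**The case against.** The strongest reply is that nothing planned is lost. The article promises 80% power and Fisher delivers 84.5% in a single look or with an O'Brien-Fleming-type interim. The stated 122 also looks as if it already allows for a conservative test. This stands. A reader might infer that the trial is underpowered, or that Fisher is a mistake, and the documents support neither. Power is lost only relative to another valid test. The one case below 80% (78.7%) needs constant Pocock bounds, which the article does not state.

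A reader might also infer that no between-arm effect is estimated at all. That goes too far: effects by factor level are planned, and two reported proportions give the point difference by subtraction. What is not named is an overall effect measure with its interval. The full protocol or SAP, not shown, may supply it; if so, that half of the point is settled.

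Nor should the overlap of Wilson intervals be pressed. It occurs at the first significant table for each laser count from 0 to 11, but these are borderline tables. At 12% v 2% and 122 per arm, a significant result with overlapping intervals has probability 20.3% out of 84.5%, about a quarter of significant results (20.3/84.5 = 24%).

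Finally, the group sequential design does not defeat the proposal, since the gain persists at smaller final-look alphas. The joint error over both looks has not been computed for Boschloo, because no boundary is given. That computation belongs to the change.

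**Conclusion.** The point holds as a cheap improvement. Fisher's test is valid and meets the power target at the design rates, but uses roughly 2.5% to 3.1% of the allowed 5% at common rates of 7% to 12%. Boschloo's test recovers 3.4 points of power at 122 per arm and 2.2 at 136 for 12% v 2%, and 5.1 points at 122 if the laser rate is 3%, which is an assumed figure. The named primary outputs also lack an overall effect with an interval.

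These figures rest on full enumeration of two independent binomials with equal arms and a single look at 5%, unless stated otherwise.

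**What to change.** Before unblinding, and preferably before the interim comparison, amend the Analytic plan for the primary outcome:

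- Name Boschloo's exact test as the primary test, at the final-look alpha of the group sequential design, with Fisher's test as a sensitivity result.
- Once the boundary is written down, check by enumeration that the joint error over both looks is at most 5%.
- Name the overall risk difference with a Newcombe 95% interval, built from the Wilson limits already planned, as the primary effect estimate.

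The third item is worth doing even if Fisher's test is kept. The cost is a sentence or two and a short calculation, with no extra patients or data. There are two small downsides. Boschloo's test is less familiar to readers. The Newcombe interval is also not an inversion of it, so test and interval can disagree in borderline cases; the plan should say that the test decides.

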### Baseline assessment

After verification of eligibility by initial phone interview and again at the first clinic visit prior to randomization and treatment, both the patient and legal guardian are asked to provide demographic and socioeconomic information including age, race, ethnicity, gender, annual household income range, patient occupation (from those engaged in paid employment), guardian occupations, and specific insurance coverage. We also collect a complete medical history of pilonidal disease, family history of pilonidal disease, current pilonidal disease symptoms, current hygiene regime, and history of physician office visits, emergency department/urgent care visits, and inpatient hospitalizations for pilonidal disease. A sample list of the collected data points is provided in Table 2. At the initial clinic visit, a physician member of the research team (1) reviews the study protocol and procedures, (2) explains the risks and benefits of each treatment, (3) answers questions, and (4) obtains written informed consent and assent (for patients < 18 years of age). The child and legal guardian are asked to complete the age-appropriate Pediatric Quality of Life Inventory (PedsQL™) and questions about healthcare-associated disability, pain, and pilonidal disease management. The patient also completes the Child Attitude Toward Illness Scale (CATIS), and the parent and child complete the disease-related stigma scales. Patients are then randomized and informed of their treatment arm.

**Table 2 Tab2:** Sample of data to be collected

• Demographics (including age, gender, body mass index, race, ethnicity, caregiver education level, employment status, income, marital status, number of household residents)	
• Fitzpatrick skin type	
• Vital signs	
• Laboratory testing	
• Episodes of pilonidal disease	
• Surgical procedures performed for pilonidal disease	
• Symptoms	
• Medications	
• Complications (if any)	
• Readmissions	
• Recurrence	
• Days missed from work or school	
• Days missed from normal activities	
• Office visits referable to pilonidal disease	
• Emergency department visits for pilonidal disease	
• Treatment-related pain	

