### Outcomes

The primary outcome is pilonidal disease recurrence at 1 year, defined as development of a new pilonidal abscess, folliculitis, or draining sinus after treatment, which would require antibiotic treatment, additional surgical incision and drainage, or excision. Secondary outcomes include each of the following at 1 year: disability days of the patient, disability days of the caregiver, HRQOL, healthcare satisfaction, disease-related attitudes and perceived stigma, pilonidal disease-related complications, pilonidal disease-related procedures, surgical excision, postoperative complications, and compliance with recommended treatment.

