#### Follow-up at 6, 9, and 12 months

Each participant receives an email or telephone call at 6, 9, and 12 months after their initial visit. Follow-up is conducted by email/web-based survey or by phone with a member of the research team from NCH. The patient and legal guardian complete surveys assessing disability days, pain, pilonidal disease management, and emergency department/urgent care/physician office/hospital visits that occurred between follow-up assessments. At 6 and 12 months, the age-appropriate Child and Parent PedsQL™ and the CATIS are administered. At 9 months, healthcare satisfaction and disease-related stigma scales are administered.

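### PedsQL, CATIS and stigma scores are compared by Mann-Whitney tests that make no use of the pre-randomization scores: a loss of precision, not a bias

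*Protocol article*

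**What the plan says.** On the test, the Analytic plan reads: "Continuous secondary outcomes (e.g., HRQOL) will be assessed using medians and interquartile ranges and compared between groups using Mann-Whitney" U tests. The comparisons are not ranked as exploratory: "These are hypothesis-driven analyses, with the laser group expected to have less disability for both the patient and caregiver, higher HRQOL scores". Favourable differences in attitudes and perceived stigma are listed among the same expectations. No covariate or change score is named.

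On baseline data, the Baseline assessment section says "The child and legal guardian are asked to complete the age-appropriate Pediatric Quality of Life Inventory", and then "The patient also completes the Child Attitude Toward Illness Scale (CATIS), and the parent and child complete the disease-related stigma scales". Allocation follows: "Patients are then randomized and informed of their treatment arm". Each of the three instruments therefore has a score that treatment cannot have influenced.

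On timing, the Outcomes section says "Secondary outcomes include each of the following at 1 year: disability days of the patient, disability days of the caregiver, HRQOL, healthcare satisfaction", and the same list goes on to disease-related attitudes and perceived stigma. The follow-up schedule says "At 6 and 12 months, the age-appropriate Child and Parent PedsQL™ and the CATIS are administered", but for the other scales "At 9 months, healthcare satisfaction and disease-related stigma scales are administered". No 12-month stigma assessment is listed.

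Linear mixed models of the full course of these scores are also planned, but under further exploratory analyses.

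**The concern.** A two-sample Mann-Whitney test of follow-up scores has no place for a covariate. Variation between patients that was already present at entry stays in the comparison as noise. A patient's quality of life or attitude score at entry would usually predict the later score to some degree, so part of that noise could be removed with data the trial collects anyway.

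This matters because the Background names these scales among the outcomes important to patients, while the sample size was set on recurrence alone. The article gives no power for the continuous scores, so their precision depends on how they are analysed. What is at stake is the chance of detecting a moderate benefit on them and the width of the interval around it.

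**Working it through.** **Inputs from the article.** Sample size and power section: 122 evaluable per arm, 136 enrolled per arm, two-sided 5%, 80% power, recurrence 12% against 2%, drop-out 10%.

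**Inputs assumed.** The correlation r between baseline and follow-up score, and the true difference on a scale. Neither is given for these outcomes. I take r from 0.2 to 0.7 and, for illustration, a difference of 0.30 SD.

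**1. The plan's own figure.** Comparing 12% with 2% at two-sided 5% and 80% power needs 102 per arm without a continuity correction and 121 with it (122 if the final test is at 0.048 after an interim look). Then 122/0.9 = 135.6, rounded up to 136. The stated figures reproduce, so 122 per arm is a fair basis for the scores.

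**2. Unadjusted power at 0.30 SD.**
- Comparison of means: Φ(0.30 × √(122/2) − 1.96) = Φ(2.343 − 1.96) = 0.649.
- Mann-Whitney, with its efficiency of 3/π = 0.955 under normal scores: Φ(2.343 × √0.955 − 1.96) = Φ(2.290 − 1.96) = 0.63.

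**3. Baseline-adjusted.** The residual variance is multiplied by 1 − r². The effective size is 122/(1 − r²), and power is Φ(2.343/√(1 − r²) − 1.96).

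| r (assumed) | Variance cut | Effective n per arm | Power at 0.30 SD |
|---|---|---|---|
| 0.2 | 4% | 127 | 67% |
| 0.3 | 9% | 134 | 69% |
| 0.5 | 25% | 163 | 77% |
| 0.6 | 36% | 191 | 83% |

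The effective sizes are relative to an unadjusted comparison of means.

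**4. Does skew undo this?** A simulation with 122 per arm, a 0.36 SD shift and 3,000 runs per setting gave these powers (Mann-Whitney / ANCOVA / ANCOVA on ranks):

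| r | Normal scores | Scores cut off at a ceiling |
|---|---|---|
| 0.2 | 0.78 / 0.82 / 0.79 | 0.77 / 0.79 / 0.79 |
| 0.3 | 0.79 / 0.83 / 0.82 | 0.75 / 0.79 / 0.79 |
| 0.5 | 0.78 / 0.90 / 0.88 | 0.76 / 0.86 / 0.86 |
| 0.7 | 0.77 / 0.98 / 0.96 | 0.77 / 0.95 / 0.95 |

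The ceiling reduces the gain somewhat but does not remove it. In the ceiling setting, ANCOVA on raw scores does as well as ANCOVA on ranks.

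**5. Which visit.** PedsQL and CATIS have both a baseline and a 12-month score, so a 12-month adjusted analysis can be run as scheduled. Stigma has a baseline score and a last listed score at 9 months, so the same analysis can be run at 9 months but not at 12.

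**The case against.** The strongest reply is that nothing here is invalid. Under randomization an unadjusted Mann-Whitney test holds its type I error rate, and chance imbalance at baseline is already allowed for in that rate. This stands. A reader might infer that the secondary results would be biased or falsely significant, or that the primary result or sample size is affected. The article supports none of these inferences.

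A second reply is that the mixed models of the full trajectory would naturally take in the baseline score. That is fair: it would be wrong to say that the plan ignores baseline altogether. But those models are ranked as exploratory, and the hypothesis-driven comparison is the one that leaves baseline out.

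Third, Mann-Whitney is robust for bounded, skewed scores. This is true, and a reason to keep it as a sensitivity analysis. The ceiling simulation shows that robustness does not have to be paid for by dropping the baseline score.

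Fourth, a condensed article may leave covariates and interval estimates to an analysis plan that is not shown. I therefore do not treat a missing interval as a fault. The test itself, however, is stated here.

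Finally, the size rests on an unknown correlation. After a year that includes treatment and possible recurrence, r could be modest. At 0.2 to 0.3 the gain is small, and a reader should not take the figures at 0.5 or 0.6 as established.

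**Conclusion.** The point holds as a matter of efficiency in the secondary outcomes. The plan names a main comparison for three baseline-measured scales that cannot use the baseline score.

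The loss ranges from slight (4% of variance at r = 0.2) to material (36% at r = 0.6). At 0.30 SD and 122 per arm, power of about 63% becomes 67% at r = 0.2 and 83% at r = 0.6. About two points of each difference come from the efficiency of Mann-Whitney under normal scores rather than from adjustment. These figures assume normal scores, 122 analysed per arm, and correlations and a difference that the article does not supply.

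A reader might also infer that a 12-month adjusted analysis of stigma could simply be run. It could not as scheduled, because the stigma scales are last listed at 9 months. The Outcomes section and the follow-up schedule disagree on this and need to be reconciled whichever test is used.

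**What to change.** Pre-specify one main analysis for the 12-month PedsQL scores (child and parent) and the 12-month CATIS score: ANCOVA of the follow-up score on arm and the baseline score of the same instrument, with robust standard errors, reporting the adjusted mean difference and its 95% CI. Do not leave the choice of model to depend on how skewed the data turn out to be. Keep Mann-Whitney as a sensitivity analysis for these scales, and as the main test for healthcare satisfaction, for which no baseline is listed.

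For stigma, use the same model at the last scheduled assessment, which is 9 months as the schedule stands. Bring the 1-year label in the Outcomes section and the 9-month visit into line.

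For PedsQL and CATIS the cost is analysis wording only, since the scores are already scheduled at both times. The reported effect becomes a difference in means rather than a comparison of medians, and the text should say so. For stigma the cost is either a corrected time point or an added 12-month questionnaire. There was room to make the change early: Trial status reports enrolment from September 2017 and over 50 patients by 25 October 2018, so only those enrolled in the first weeks could by then have completed a year.
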